#### Planned subgroup analyses

1. The presence of a MVS ≥9 will be analyzed by (i) age <1 year, (ii) breast-feeding status, (iii) antibiotic usage and (iv) protocol compliance.

2. Duration of vomiting will be analyzed only in those patients who have had ≥3 episodes of vomiting in the 24 hours prior to enrollment.

3. Daycare and work absenteeism will only be analyzed for children who attend daycare and caregivers who work.

4. In children with rotavirus infection, an interaction term will be added between treatment and rotavirus positivity in a logistic regression model. The independent variables in the model will be (i) treatment group, (ii) rotavirus positivity (yes/no) and (iii) the interaction between treatment group and rotavirus positivity.

5. Fecal sIgA levels will be subanalyzed based on the mother’s breast-feeding status.

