### Intervention

Informed consent will be obtained from each participant’s legally authorized guardian prior to enrollment into the study. Once consent is provided, the first dose will be administered in the ED. The sachet’s contents will be sprinkled into 30 mL of oral rehydration solution (ORS). Caregivers will receive instructions on study drug administration, completion of study forms, what and how much fluid to drink, criteria for seeing a health care practitioner or returning to the ED [see Additional file 1] and standardized AGE discharge instructions.

All patients will take one sachet every 12 hours for 5 days, at meal time, even once symptoms have resolved. The dose will be repeated once should vomiting occur within 15 minutes of medication administration. Children who are hospitalized will continue as per study protocol.

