### Randomization

#### Sequence generation

We used http://www.randomize.net to produce the study randomization lists stratified by site. The lists were sent to the central pharmacy at ACH where an independent research pharmacist prepared consecutively numbered kits according to the randomization schedule. The kits were couriered directly to the sites using insulated shipment containers and temperature monitors.

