### Concomitant medications

The concomitant administration of antibiotics is permitted as probiotics remain effective when given concomitantly with antibiotics [43]. Their use is at the discretion of the child’s treating physician. Similarly, antipyretics, anti-emetics, and other medications may be administered. ORS will be provided during the ED visit. Discharge instructions will be provided.

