### Outcomes

#### Primary outcome (clinical)

The primary outcome is the development of moderate to severe disease in the 2 weeks after the index ED visit as measured by the MVS (Table 1) [44]. The original 20 point Vesikari Score, which has been employed as a dichotomous variable in many clinical studies [45-53], correlates with other meaningful measures such as caregiver anxiety, helplessness, stress, [54] parental worry, behavioral changes, and impact on the parents’ daily activities and distress [55]. However, percent dehydration, an element of the original score, is challenging to quantify due to difficulties in collecting follow-up weights, determining when rehydration has occurred, and the variation related to timing of voiding, stooling, eating, and drinking. Thus, this element is omitted or incorrectly assigned in many studies. The modified score includes an important and easy to obtain outcome that reflects global disease severity - need for unscheduled healthcare provider visits within 2 weeks of the index visit [44]. This is supported by evidence that the utilization of professional medical care correlates with disease severity [54].

**Table 1 T1:** Modified Vesikari Scale

**Points**	**0**	**1**	**2**	**3**
**Diarrhea duration**	0	1 to 96 hours	97 to 120 hours	≥121 hours
**Maximum number of diarrheal stools/24-hour period**	0	1 to 3	4 to 5	≥6
**Vomiting duration (d)**	0	1 to 24 hours	25 to 48 hours	≥49 hours
**Maximum number of vomiting episodes/24-hour period**	0	1	2 to 4	≥5
**Maximum recorded fever**	<37.0˚C R	37.1 to 38.4˚C R	38.5 to 38.9˚C R	≥39.0˚C R
**Future healthcare visit**	0%	-	Primary care	Emergency department
**Treatment**	None	Rehydration	Hospitalization	-

R, rectal.

Follow-up will occur daily until both the diarrhea and vomiting have resolved. On Day 14 each variable is assigned a score for the entire study period (Time 0 to Day 14); each patient gets a single total score for the study. Variables are scored based on the worst 24-hour period or on the total duration of symptoms or are based on the occurrence of an outcome.

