### Data retrieval

1. Daily Telephone/Electronic Survey Communication: At the index visit, caregivers will be asked their preferred method of communication - electronic versus telephone. Caregivers will be contacted daily by the identified method until both the diarrhea and vomiting have resolved. A standardized collection form will be employed. Detailed questioning will follow positive responses. Compliance will be assessed on Day 5. To maximize validity, caregivers will be reminded of the importance and method of administering the probiotic/placebo.

2. Chart Review: We will verify data regarding revisits, intravenous hydration, hospitalization, and microbiology testing using each center’s medical record database.

3. Database Reviews: Provincial databases and Canadian Institute for Health Information databases will be employed to verify future health care provider use.

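### Protocol compliance, measured on Day 5, is listed as a subgroup for the primary outcome, so treatment comparisons within compliers are not randomised and can show a false effect

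*Protocol article*

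**What the plan says.** Under Planned subgroup analyses, the first item divides the primary outcome by age under one year, breast-feeding status, "iii) antibiotic usage and (iv) protocol compliance". All four are listed alike and none is given a time of measurement.

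Other sections fix the timing of compliance and leave that of antibiotic use open:

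- Data retrieval: "Compliance will be assessed on Day 5".
- Intervention: "All patients will take one sachet every 12 hours for 5 days, at meal time, even once symptoms have resolved". The first dose is given in the emergency department.
- Primary outcome (clinical): "The primary outcome is the development of moderate to severe disease in the 2 weeks after the index ED visit".
- Concomitant medications: "The concomitant administration of antibiotics is permitted as probiotics remain effective when given concomitantly with antibiotics". The next sentence leaves the decision to the treating physician ("Their use is at the discretion of the child" and so on).
- Statistical analysis: every analysis except that of adverse events is to follow intention to treat.

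The rotavirus item begins: "In children with rotavirus infection, an interaction term will be added between treatment and rotavirus positivity in a logistic regression model". It then lists treatment group, rotavirus positivity (yes/no) and their interaction as the independent variables.

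**The concern.** Randomisation balances the arms within a subgroup only if membership is fixed before allocation, or at least cannot be affected by it. Age meets that condition. Compliance over a five-day course does not.

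The article's own rules tie compliance to the course of illness, and so to the outcome. A dose vomited within 15 minutes is repeated only once, and vomiting supplies two items of the score. Sachets continue after recovery, when a caregiver's motivation may differ. Intensive care admission leads to withdrawal from the study, and an intentionally unblinded child stops study therapy. If the product alters symptoms or tolerability, compliers in the two arms are selected differently.

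What is at stake is interpretation. If the primary result were null, a benefit in compliant children could be reported as a pre-specified subgroup finding, although it would rest on a comparison that randomisation does not protect.

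**Working it through.** **Timing, side by side.** The course runs over Days 0 to 5, compliance is recorded on Day 5, and the outcome covers Time 0 to Day 14. The subgroup variable is thus formed after allocation and inside the outcome window. That is enough to establish the point. The arithmetic below only shows how large the distortion could be.

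**Inputs from the article.** The control event rate is 25%, and 886 children are randomised 1:1, or 443 per arm. The article gives no figure for compliance or for any subgroup effect. Its unadjusted sample size is not in dispute and reproduces: for 25% v 15%, two-sided 0.05 and power 0.90, n = (1.960·√(2·0.20·0.80) + 1.282·√(0.25·0.75 + 0.15·0.85))² / 0.10² ≈ 334.2, so 335 per arm and 670 in total.

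**Assumptions (not in the article).** There is no treatment effect. Half the children have high latent severity with risk 40% and half have low severity with risk 10%, so both arms have 0.5·0.40 + 0.5·0.10 = 25%. Compliance is 90% in mild children in both arms and 80% in severe children on placebo. Only compliance in severe children on probiotic (c) varies.

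Risk among compliers = (c_severe·0.40 + c_mild·0.10) / (c_severe + c_mild).

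Placebo: (0.80·0.40 + 0.90·0.10) / 1.70 = 0.41/1.70 = 24.1%.

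| c, severe on probiotic | Probiotic compliers | Difference from placebo | Two-sided rejection rate at nominal 5% |
|---|---|---|---|
| 80% (same as placebo) | 0.41/1.70 = 24.1% | 0 | 5.0% |
| 70% | 0.37/1.60 = 23.1% | −1.0 point | 6.2% |
| 60% | 0.33/1.50 = 22.0% | −2.1 points | 10.2% |
| 50% | 0.29/1.40 = 20.7% | −3.4 points | 18.6% |

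Rejection rates use a pooled two-proportion z-test with 443 per arm times the proportion compliant. Non-compliers show the opposite error: at c = 60%, (0.40·0.40 + 0.10·0.10)/0.50 = 34.0% on probiotic against (0.20·0.40 + 0.10·0.10)/0.30 = 30.0% on placebo, or +4.0 points. If the dependence on arm ran the other way, the signs would reverse.

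**A second model.** Let severity U be standard normal, let the event occur when U plus noise exceeds its 75th percentile, and let logit(compliance) = 1.4 − bU. With b = 0.2 on placebo and 0.4 on probiotic, the false benefit among compliers is 0.8 to 1.4 points as the noise SD runs from 1.5 down to 0.25. With b = 0.2 v 0.8 it is 2.4 to 4.4 points. Overall compliance in the latter case is 80% v 78%, so similar compliance in the two arms does not show that bias is absent. With equal b it is zero.

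**Antibiotics, if use after randomisation counts.** Under the same null, assume use of 15% (severe) and 5% (mild) on probiotic against 10% in both groups on placebo. Users show (0.15·0.40 + 0.05·0.10)/0.20 = 32.5% v (0.10·0.40 + 0.10·0.10)/0.20 = 25.0%, a false +7.5 points with about 44 users per arm and a rejection rate of 12.2%. Non-users differ by −0.8 points. If the subgroup is fixed before randomisation, the expected difference is 0.

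**The case against.** The strongest reply is that the bias needs membership to depend on arm, and nothing in the article shows that it does. The trial is double-blind, the powders are described as identical in appearance, taste, texture and smell, and a pilot found no side effects at this dose. The upper end of the range needs a severity–compliance slope four times as steep on probiotic. This stands as far as size is concerned: a range that includes zero is all the article supports. It does not remove the defect, because blinding cannot stop an active product from changing symptoms and, through them, dosing.

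A reader might infer more in four places, and the article does not support it.

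- *The antibiotic subgroup is certainly post-randomisation.* No timing is given. Study population accepts antibiotic-associated diarrhoea as a diagnosis, so a baseline reading is open, while Concomitant medications leaves a later one open. The window is undefined.
- *Subgroups other than rotavirus will be tested separately, without an interaction test.* The article does not say so, and the test for each subgroup is ordinary content of an analysis plan that is not shown.
- *The rotavirus interaction cannot be estimated.* That follows only if the lead-in is read literally. The same item lists positivity as yes/no, so both groups are evidently meant. It is a drafting slip.
- *The rotavirus model is faulty because it omits site.* Randomisation lists were stratified by site, and the main tests respect that. Leaving site out of an exploratory model is a matter of preference.

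**Conclusion.** The point holds for compliance with certainty: a variable recorded on Day 5 is listed beside baseline factors, and comparing arms within its levels departs from the article's own intention-to-treat statement. For antibiotics it holds conditionally, if courses begun after randomisation are counted.

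Under a true null, the false difference among compliers runs from 0, through about 1 point, to about 4 points. These figures rest on assumed compliance patterns and should not be read as a prediction that the trial will show such a bias.

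Nor does the point reach the main result. The site-stratified Mantel-Haenszel test of the primary outcome and the sample size of 886 are untouched. This is a correction that should be made to a supporting analysis.

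**What to change.** 1. Remove protocol compliance from the subgroup list. Report it only as a supplementary per-protocol analysis, labelled as a non-randomised comparison. Any complier-effect estimate must state its threshold for receipt and its exclusion assumption. Because the first dose is given in the emergency department, nearly every child allocated to probiotic receives some product, so dividing by the difference in any receipt would return roughly the intention-to-treat estimate. If receipt means completing the course, partial dosers have still taken active product and the exclusion assumption fails.
2. Define the antibiotic subgroup as use at or before randomisation.
3. Reword the rotavirus item so that the interaction model is fitted in all children with a rotavirus result.

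The cost is wording and a little analysis time, with no new data on compliance and no change in sample size. The one real downside is a smaller antibiotic subgroup.

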### Safety

The Data Safety Monitoring Committee (DSMC) will meet after 200 and 500 patients to review enrollment, study procedures, form completion, data quality, loss to follow-up, drop-in rate, and interim safety and efficacy results. The analyses will test the hypothesis that the probability of developing moderate to severe AGE in the probiotic arm is equal to that in the placebo arm. Conservative O’Brien-Fleming monitoring boundaries, implemented using the Lan-DeMets alpha-spending function approach, will be used as guidelines for early stopping for safety or efficacy. Based on trends and adverse events, the DSMC may decide to meet sooner than planned using boundaries adjusted accordingly. Because this trial involves children under the age of 6 months, the DSMC has approved a plan to complete an interim safety analysis on the first 20 subjects enrolled under 6 months of age. All serious adverse events will be reported within 24 hours to the DSMC and based on these reports; the DSMC may decide to conduct a safety analysis before the full 20 subjects have been enrolled in this age group. Otherwise, a blinded analysis will be conducted after the 20 subjects <6 months of age have been enrolled. This data will be unblinded if the DSMC deems it necessary to conduct an unblinded interim safety analysis. The results of this analysis will be communicated to Health Canada at the discretion of the DSMC chair should any concerns be identified. The DSMC consists of a biostatistician ([name]-Ottawa), and two physicians with RCT expertise (Drs. [name]-Minnesota and [name] (Chair) -Winnipeg).

An adverse event has been defined as any unfavorable or unintended clinical or other occurrence during the study period that may or may not be the result of participation in the research study.

Expected adverse drug reactions/events include the following, which were deemed to be part of the natural history of the underlying disease process:

1. hospitalization

2. future healthcare provider visit, ED return visit

3. IV rehydration

4. abdominal pain, distension

5. vomiting, diarrhea, fever, flatulence

Because expected adverse events are part of the natural history of AGE and diarrheal illness in children, they will not need to be reported as adverse events. This information will be recorded in normal study data collection processes. Any serious adverse event (SAE) that occurs after the first sachet administered will be reported to the Research Ethics Board (REB) and the study subject will be followed until the conclusion of the event. Any serious adverse event to the natural health product will be reported to Health Canada. An SAE has been defined as any of the following:

1. results in death.

2. is life-threatening. This refers to an event in which the patient was at immediate risk of death; it does not refer to an event that might have caused death had it been more severe.

3. results in a persistent or significant disability/incapacity.

4. is medically significant. Important medical events that may not result in death, be life-threatening, or require hospitalization may be considered SAEs when, based upon appropriate medical judgment, may jeopardize the patient and may require medical or surgical intervention to prevent one of the outcomes listed in this definition.

Unblinding should only occur in the event that there is clinical concern regarding the possibility of bacteremia/septicemia or when it is felt by the treating physician that unblinding would alter the clinical care being provided. All patients whose therapy is intentionally unblinded will discontinue the experimental therapy. Approval from the principal investigator or designate will be obtained prior to unblinding. If the principal investigator cannot be reached, unblinding can be performed and the principal investigator informed within 24 hours via email or telephone.

Subjects will be withdrawn from the study if:

1. after enrollment they are determined to meet any of the exclusion criteria.

2. the subject is admitted to an intensive care unit.

3. it is deemed by the treating physician that the child’s health may be jeopardized by continued participation in the study.

4. the patient’s caregivers wish to withdraw their child for whatever reason.

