#### Safety

To determine if short course probiotic administration to young children with AGE is associated with an increase in minor side effects, groups will be compared regarding the development of any side effects with particular attention paid to bloating or abdominal distention (grouped for analysis), duration of fever, and buttock rash.

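### Hospitalization is exempt from adverse-event reporting without an explicit link to the index gastroenteritis and is absent from an SAE definition that presupposes it, so expedited reporting of an admission for non-life-threatening invasive infection is left to judgment

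*Protocol article*

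**What the plan says.** All the relevant rules stand in the protocol article's Safety section that covers the DSMC and adverse events.

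- **Adverse event.** The definition is broad: "An adverse event has been defined as any unfavorable or unintended clinical or other occurrence during the study period", whether or not it results from taking part in the study.
- **Expected events.** The list is introduced by "Expected adverse drug reactions/events include the following, which were deemed to be part of the natural history of the underlying disease process". Its first entry reads "1. hospitalization", with nothing added about cause. Later entries include return visits, intravenous rehydration and fever, again without a cause.
- **Exemption.** Of these expected events the section says "they will not need to be reported as adverse events". It adds that they are captured through ordinary study data collection.
- **SAE definition.** Four numbered criteria: death, a threat to life (narrowed to immediate risk of death), persistent or significant disability, and medical significance. The fourth begins "Important medical events that may not result in death, be life-threatening, or require hospitalization may be considered SAEs when" and goes on to require medical judgment. It refers back to the outcomes that the definition lists.
- **Routes.** SAEs go to the DSMC within 24 hours and to the Research Ethics Board. SAEs to the product also go to Health Canada.
- **Unblinding.** The same section says "Unblinding should only occur in the event that there is clinical concern regarding the possibility of bacteremia/septicemia", or where the treating physician thinks that knowing the allocation would change care.

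**The concern.** Two statements do not fit together. The fourth SAE criterion is a residual category: it catches important events that miss the other criteria, and it names needing hospitalization as one of those other criteria. No such criterion is in the list. A site reading the definition cannot tell whether hospitalization was left out on purpose, because admissions are common in this illness, or was lost by mistake.

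The expected-event list does not settle it. Exempting admissions for gastroenteritis is sensible, since they are part of the disease and of the primary outcome scale. But the list names hospitalization and fever without saying that the exemption ends where the index illness ends.

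This matters because the only reporting route with a stated time limit runs through the SAE definition. The DSMC may bring forward its safety analysis of infants under 6 months on the strength of SAE reports. Invasive bacterial infection is the one clinical event that the unblinding rule names, and it would typically come to notice as fever and an admission, both on the exempt list.

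**Working it through.** No sample size, rate or error level enters, so there is nothing to compute. The check sets the rules side by side and follows one case through them.

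**Comparing the rules**

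| Question | Expected-event list and exemption | SAE definition |
|---|---|---|
| Is hospitalization named? | Yes, as the first item | Not as a criterion; only inside the wording of criterion 4 |
| Is a cause stated? | No; the rationale is that the events were "which were deemed to be part of the natural history of the underlying disease process" | Not applicable |
| Result for an admission | Need not be reported as an adverse event | An SAE only if another criterion is met |

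The SAE criteria are numbered 1 to 4 without a break, so the missing item is not a gap left by text extraction.

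**Following one case.** Take a child admitted with an invasive infection, not at immediate risk of death and without lasting disability.

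1. The admission and the fever are both on the expected list. Read literally, neither has to be reported as an adverse event.
2. The infection is not on the list. Under the broad definition it is an adverse event, and the exemption does not reach it.
3. SAE criteria 1 to 3 are not met. Criterion 2 is confined to immediate risk of death.
4. Criterion 4 may apply, but its wording is permissive and turns on judgment.
5. If criterion 4 is not invoked, no text sends the case to the DSMC within 24 hours or to the Research Ethics Board.

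**Varying the case.** If the infection puts the child at immediate risk of death, criterion 2 makes it an SAE without any judgment about medical significance. The gap is therefore confined to serious but not immediately life-threatening infection, and to other admissions unrelated to gastroenteritis.

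**What is still captured.** The Data retrieval section has hospitalization and microbiology testing verified by chart review. Hospitalization scores points on the Modified Vesikari Scale (Table 1), and the Clinical part of the Statistical analysis section evaluates it as a dichotomous outcome.

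**The case against.** The strongest reply is that the exemption carries its own limit. It is justified by the natural history of gastroenteritis, so an admission for something else falls outside it. A conscientious site would also report sepsis as a medically significant event, because it may need intervention to prevent a worse outcome. And this is a condensed article, whose full protocol may hold more detailed SAE rules.

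Much of this stands. A reader might infer that hospitalization and fever of any cause are expressly exempt, so that an admission for invasive infection need not be reported at all. The documents do not support that. The rationale points to gastroenteritis, the infection itself is never exempted, and the life-threatening form is plainly an SAE.

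Nor does it follow that the DSMC would be blind to such cases. Its reviews after 200 and 500 patients, and the analysis of the first 20 infants under 6 months, are not limited to SAEs. The contents of its reports are reasonably left to other documents.

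It is also tempting to see a conflict with the safety outcome, which compares side effects "with particular attention paid to bloating or abdominal distention (grouped for analysis), duration of fever, and buttock rash". There is none: exempt events are still recorded as study data and can be compared between groups.

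What the reply does not remove is the contradiction within the SAE definition. The article states the rule in full and states it inconsistently, which is different from leaving detail to a longer document. A limit that has to be inferred from a rationale is also a weak instruction for five sites.

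**Conclusion.** The inconsistency is real and should be corrected. As written, expedited reporting of an admission for a non-life-threatening invasive infection depends only on the discretionary fourth criterion. What is at risk is assured prompt notice to the DSMC and the Research Ethics Board, and to Health Canada where the product is implicated. The data themselves are not lost.

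No number of affected children can be given. The documents state no expected admission rate for this trial and no rate of admissions unrelated to gastroenteritis. A reader might apply the 19% clinical sepsis quoted in the Background to an assumed number of admissions. That figure describes children hospitalized with gastroenteritis and is cited as disease burden. It is not a rate of infection in this emergency department population, which excludes children with indwelling vascular lines or immunodeficiency, and it does not count unreported cases.

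The conclusion assumes that the reporting rules sites follow match the article. If the full protocol already limits the exemption and lists hospitalization among the SAE criteria, only the article's wording needs correcting.

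**What to change.** Reconcile the expected-event list, the exemption and the SAE definition in one amendment:

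1. Limit the exemption explicitly to listed events that are attributed to the index gastroenteritis.
2. State in the SAE definition whether hospitalization not attributable to the index gastroenteritis is an SAE, so that the list and the wording of criterion 4 agree.
3. State there whether suspected or confirmed bacteremia or sepsis is an SAE, so that classification no longer rests on criterion 4 alone.

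The cost is amendment wording, a note to the five sites and, depending on the choices made, a few additional SAE reports. Admissions are already recorded and chart-verified, so no new data collection is needed. Sample size and analysis are unaffected.
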